### **Objective 3 -Determine preliminary intervention and effectiveness outcome utility**

This pilot study will collect data on one service outcome, patient management. It will be verified with a checklist submitted to participating physicians to allow them to record, per patient encounter, if they received the I-Score results on time, if they reviewed them prior to or during the clinic visit, if they were discussed during the visit, and if the I-Score identified concerning barriers. Then, they will check off any clinical actions that were taken based on the I-Score results or any related patient-provider discussion (e.g., recording issues in medical notes, referring to another health professional, ordering a test, changing a medication or treatment, providing advice or education). See the Appendix for the physician checklist.

The patient outcomes assessed in this pilot are barriers to adherence, adherence and viral load. Barriers to ART adherence will be assessed at T1, T2, and T3, with our previously described ePROM. Adherence will be examined with the Self-Rating Scale Item (SRSI) (Feldman et al., 2013) at T1, T2, and T3. It is a one item measure of treatment adherence (i.e. “Rate your ability to take all your medications as prescribed” [over the past 4 weeks], rated on a 6-point scale (i.e. Very poor, Poor, Fair, Good, Very good, and Excellent). Viral load, a clinical indicator of viral activity (e.g., infectiousness) and treatment response, will be treated as a dichotomous variable based on whether, as indicated in the patient’s medical file, the HIV RNA viral load is detectable (over 50 copies), or not. Undetectability is a goal of HIV treatment. The most recent viral load test result at T1 and T3, will be collected.

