Regarding the patient outcomes of Objective 3, barriers to adherence and adherence will be summarized with the minimum, the maximum, the mean, and the standard deviation. Viral load will be reported by absolute and relative frequencies, as it is considered a dichotomous variable. For the service outcome obtained from the physician checklist, we will report the proportion of clinic visits when physicians took action based on the I-Score results, among the visits where an adherence barrier of concern was identified by physicians. Proportions will be reported for T1, T2 and T3 and globally, across time periods. To evaluate evidence of a statistically significant difference in our chosen effectiveness outcomes, we will run a Student's paired t-test for barriers to adherence and adherence and a McNemar test for viral load, between T1 and T3. To complete the analysis of the service outcome, we will use a logistic regression model, considering only the visits where an adherence barrier of concern was identified by physicians. The dependent variable is the binary variable of whether or not an action was taken by physicians and the independent variable is the time, considered as a factor with three independent levels (T1, T2 and T3). We will test the null hypothesis that time has no effect on the probability of taking action, with a t-test on the regression coefficient. We will conclude the analysis by testing the null hypothesis of equality of proportions between all pairwise combinations of time points, with a Student's t-test between two proportions, performing a Bonferroni correction for multiple tests. For all analyses, a significance level of 5% will be adopted.

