**Yes**

**No**

Receive the I-Score results on time (prior to or during the visit)?

☐
☐

Review the I-Score results prior to or during the visit?

☐
☐

Discuss the I-Score results with your patient?

☐
☐

Identify an adherence barrier of concern with the I-Score results?

☐
☐

**Based on the I-Score results, did you do any of the following?  
(Check all that apply)**

Record issues in your medical notes

☐

Provide advice, information, or education

☐

Refer the patient to another health or social service provider

☐

Order a test

☐

Modify a medication or treatment

☐

Other:

☐

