**No/no action was required**

☐

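### The only service outcome is conditioned on a physician's own tick made after the intervention, so it can rise because flagging became more selective while actions per visit stay flat or fall

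*Protocol*

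**What the plan says.** In the protocol's Quantitative analysis section, the service outcome is "the proportion of clinic visits when physicians took action based on the I-Score results", taken "among the visits where an adherence barrier of concern was identified by physicians". It is reported at T1, T2 and T3 and overall. A logistic regression of action (any versus none) on time follows, "considering only the visits where an adherence barrier of concern was identified by physicians", and then pairwise comparisons of time points with a Bonferroni correction.

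The data source is described under Objective 3: "It will be verified with a checklist submitted to participating physicians to allow them to record, per patient encounter" whether results arrived, were reviewed and were discussed, whether they showed concerning barriers, and what was done. The listed clinical actions are "recording issues in medical notes, referring to another health professional, ordering a test, changing a medication or treatment, providing advice or education".

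The form in the Appendix (Physician checklist per HIV patient visit) has a yes/no item "Identify an adherence barrier of concern with the I-Score results". The action boxes follow, the first being "Record issues in your medical notes", and there is a closing option "No/no action was required". The action boxes are not restricted to visits with a yes on the flag item.

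The Patient management row of Table 3 gives p ≤ 0.05 as the threshold for success. It states no target proportion and no direction. The protocol gives no expected flagging or action rate.

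**The concern.** Identifying a barrier from the I-Score is one of the steps the intervention is meant to bring about. Conditioning on it makes the analysis set a post-intervention subset, chosen by the person whose behaviour is being measured. Two consequences follow.

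- **The comparison over time mixes two things.** If physicians become more selective between T1 and T3 about what they call a concern, the conditional proportion can rise with no more management than before. Visits where nothing was flagged leave the denominator, whether because the results were not reviewed or because they were reviewed and judged unremarkable. Any action ticked at those visits is lost too.
- **The bar for action is low.** A medical note alone scores the same as a referral, a test or a change of treatment. A proportion that starts high leaves little room for a time effect to show.

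Objective 3 asks whether the intervention shows promise and whether the chosen outcomes are useful for a definitive trial. A service outcome that can move opposite to the number of actions is a poor basis for either answer, and a non-directional p ≤ 0.05 criterion would record such a movement as success.

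**Working it through.** The protocol has no figure for this outcome to reproduce. The check is whether the defined proportion can move against the number of actions, and how high it is likely to sit.

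**Inputs from the protocol:** 30 patients and three visits each, so at most 30 visits per time point; 5% significance level; three pairwise comparisons, so the Bonferroni level is 0.05/3 = 0.0167.

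**Assumed inputs:** flagged visits and actions per time point; every patient attends with a completed I-Score; no action is ticked at an unflagged visit.

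**1. Can the outcome rise while actions fall?**
Planned outcome = visits with action ÷ flagged visits. Comparison = visits with action ÷ all visits.

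| Case | T1 planned | T3 planned | T1 all visits | T3 all visits |
|---|---|---|---|---|
| A | 11/22 = 50% | 10/11 = 91% | 11/30 = 37% | 10/30 = 33% |
| B | 16/20 = 80% | 8/8 = 100% | 16/30 = 53% | 8/30 = 27% |
| C | 18/24 = 75% | 9/10 = 90% | 18/30 = 60% | 9/30 = 30% |

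Yes. In case A the flagging rate halves, from 22/30 = 73% to 11/30 = 37%, and that drives the rise.

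**2. Would the planned tests call it significant?**
Case A, logistic coefficient for T3 versus T1, with visits treated as independent:
- log odds ratio = ln(10/1) − ln(11/11) = 2.303
- standard error = √(1/11 + 1/11 + 1/10 + 1/1) = √1.282 = 1.132
- ratio = 2.303/1.132 = 2.03, giving p = 0.042 on a normal reference

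The plan names a t-test on the coefficient. On these 33 visits alone (22 + 11 − 2 = 31 degrees of freedom) that gives p = 0.051. Once T2 visits are in the model the value falls below 0.05: with 15 flagged T2 visits, for example, 48 − 3 = 45 degrees of freedom and p = 0.048. Case A is therefore borderline at 5%.

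Fisher's exact test gives p = 0.027. That does not reach 0.0167, so case A would not pass the pairwise step. Cases B and C are not significant (Fisher p = 0.29 and 0.64), but their reported proportions still rise while actions per visit halve.

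**3. How close to a ceiling?**
If a note and any other action are independent given a flag, P(any action) = 1 − (1 − P(note)) × (1 − P(other)).
- P(note) = 0.3, P(other) = 0.2: 1 − 0.7 × 0.8 = 44%
- P(note) = 0.7, P(other) = 0.5: 1 − 0.3 × 0.5 = 85%
- P(note) = 0.9, P(other) = 0.2 to 0.7: 92% to 97%

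The ceiling is a risk if charting is near-routine; it is not forced. If it occurred, power would be poor: for 90% versus 99% at the 5% level, 33% with 30 flagged visits per time point and 14% with 10.

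**The case against.** **Conditioning on a concern is defensible.** Where nothing needs managing, no action is the right result. In case A, fewer flags with a higher response to each could be genuine success. This stands, and it is a reason to keep the planned proportion. It does not rescue that proportion as the only measure, because on its own it cannot separate this reading from more selective flagging.

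**Failure to use the I-Score is measured elsewhere.** The fidelity outcome sets 90% physician review before or during the visit. This also stands for unreviewed visits. It does not cover visits that were reviewed but not flagged, or actions at unflagged visits.

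**Counting a chart note is an explicit choice.** Excluding notes from the definition would be a matter of preference. Showing note-only visits separately is enough.

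**A denominator from the patient's own I-Score needs a cut-off that does not exist yet.** The protocol says that scoring and interpretation details are still to come. It can therefore be at most an addition.

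**A stronger inference to avoid.** A reader might infer that the outcome must sit near 100% whatever physicians do. The documents do not support that: the checklist offers "No/no action was required", so a flagged visit can score zero, and no expected rate is given.

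**Stakes.** This is a secondary objective in a one-arm pilot whose design mainly observes effectiveness data. That limits the weight of the point.

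**Conclusion.** The point holds in this form: the proportion and its time test can rise through changed flagging while actions per visit stay flat or fall, and Table 3 would accept p ≤ 0.05 in either direction as success. The definition establishes that possibility; its size cannot be known in advance. The 41-point rise in case A (50% to 91%), against a fall of about 3 points in actions per visit, rests on invented counts. Its significance is borderline for the time coefficient and absent at the Bonferroni level. Proneness to a ceiling is a secondary concern that depends on how routinely flagged barriers are charted. The definition does not need replacing; the proportion should not stand alone. It is worth correcting before T1, because this is the only service outcome and it is meant to inform the definitive trial.

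**What to change.** In the Quantitative analysis section, keep the planned proportion and add:

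1. At T1, T2 and T3, report (i) flagged visits among all visits with a completed I-Score and (ii) visits with action among all visits with a completed I-Score.
2. Run the time model on (ii) as well as on the conditional proportion.
3. Show visits whose only action was a medical note as a separate row.
4. State that a significant time effect in the conditional proportion will not be read as changed patient management unless (i) and (ii) support it, and align the Patient management row of Table 3 with this.

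Optionally, add a sensitivity analysis with visits where the patient's own I-Score reports a barrier as denominator, provided the cut-off is fixed with the scoring rules before T1.

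**Cost:** a change of protocol wording and a few more rows of analysis. The checklist items and I-Score completion are already collected. The action rate on the all-visits denominator will be lower. Row (ii) can also fall because barriers truly improve, so the three rows have to be read together.

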## Aim and objectives

With the present mixed method pilot study, drawing on implementation science, the aim is to develop the methods and tools necessary to undertake a more robust evaluation of the implementation and effectiveness of the I-Score ePROM-within-Opal innovation (henceforth, the I-Score intervention) in routine HIV care with individuals on ART. This study's primary objectives are to evaluate perceptions of the I-Score innovation (Objective 1) and evaluate the implementation strategy (Objective 2) in terms of recommended implementation science metrics for patient-reported outcome measure initiatives in routine care (Stover et al., 2020). Its secondary objective (Objective 3) is to determine if the intervention shows promise and the chosen outcomes are useful, by observing collected data on select effectiveness outcomes (patient and service outcomes).

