## Study metrics and instruments

Details on the constructs assessed; the instruments and metrics used; the chosen thresholds for success, if applicable; the participant group contributing data; and the timing of data collection are presented in Table 2. Many of the chosen metrics are based on those recommended by Stover et al. (2020). Importantly, the authors emphasize the need to standardize evaluation metrics in patient-reported measure implementation and to distinguish between those used to assess perceptions of the innovation and those used to assess the implementation strategy. Not meeting the set thresholds for success, in this study, will signify that modifications are necessary before proceeding to a definitive trial (Thabane et al., 2010).

Table 1. Schedule of study procedures for participants

| Procedure                                                  | Timeline               |                        |                        |                        |
|------------------------------------------------------------|------------------------|------------------------|------------------------|------------------------|
|                                                            | Prior to study start   | Study start (baseline) | Month 3                | Month 6                |
| Be screened and/or consent                                 | Patients
Physicians |                        |                        |                        |
| Attend educational meeting                                 | Physicians             |                        |                        |                        |
| Receive training on the I-Score measure and Opal           | Patients
Physicians | Patients
Physicians | Patients
Physicians | Patients
Physicians |
| Complete the I-Score measure via Opal                      |                        | Patients               | Patients               | Patients               |
| Examine the I-Score measure results via the ORMS dashboard |                        | Physicians             | Physicians             | Physicians             |
| Attend HIV patient-physician visit (online or in person)   |                        | Patients
Physicians | Patients
Physicians | Patients
Physicians |
| Complete the post-visit checklist                          |                        | Physicians             | Physicians             | Physicians             |

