|                         | Ensure open channels of communication with time and space for clinicians to criticize and feedback on the PROM process | Process: Reflecting & evaluating | -                                   | Plan: Organize clinician implementation team meetings                                                                                                                                                                                                                    |
|                         | Implementation leads must consider feedback and use it to develop the process                                          | Process: Reflecting & evaluating | -                                   | Quality management: Conduct cyclical small tests of change

Building on feedback received from patients and physicians and the Application Manager's field notes, we will use a rapid-cycle evaluation approach, using the CFIR, to improve implementation. |

*Note.* PROM = patient-reported outcome measure; CFIR = Consolidated Framework for Implementation Research; \* Reproduced or adapted from Foster et al. (2018); \*\* Based on Damschroder et al. (2009); \*\*\* Based on the taxonomies of Powell et al. (2012, 2015).

Table 3. Implementation science metrics and effectiveness outcomes collected for the pilot study.

| Objective                                                                                   | Construct                 | Data collected                                                                                              | Threshold for success | Participant group |            | Timing     |
|---------------------------------------------------------------------------------------------|---------------------------|-------------------------------------------------------------------------------------------------------------|-----------------------|-------------------|------------|------------|
|                                                                                             |                           |                                                                                                             |                       | Patients          | Physicians |            |

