| Objective 3
– Determine preliminary intervention effectiveness & outcome measure utility | Patient management        | Checklist of physician actions following review of the I-Score results                                      | $p \leq 0.05$         | -                 | ✓          | T1, T2, T3 |
|                                                                                             | Barriers to ART adherence | The I-Score PROM                                                                                            | $p \leq 0.05$         | ✓                 | -          | T1, T2, T3 |
|                                                                                             | Adherence to ART          | Self-Rating Scale Item (Feldman et al., 2013)                                                               | $p \leq 0.05$         | ✓                 | -          | T1, T2, T3 |
|                                                                                             | Viral load                | The HIV RNA viral load, as indicated in the patient's medical file (> 50 copies = detectable)               | $p \leq 0.05$         | ✓                 | -          | T1, T3     |

PROM: patient-reported outcome measure; ART: antiretroviral therapy. \* Qualitative data include the Application Manager's notes (T1-T3), the qualitative interviews with patients and the focus groups with physicians (T2, T3).

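### Table 3 makes an undirected p ≤ 0.05 the success threshold for the Objective 3 outcomes: the favourable direction is left unstated, and the p-value cannot show whether the outcomes are useful

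*Protocol*

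**What the plan says.** The Aim and objectives section sets Objective 3 as to "determine if the intervention shows promise and the chosen outcomes are useful, by observing collected data on select effectiveness outcomes". Table 3 labels the objective "Determine preliminary intervention effectiveness & outcome measure utility". In the column headed "Threshold for success", the rows for barriers to ART adherence, adherence and viral load contain only p ≤ 0.05, and so does the row for patient management.

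The Quantitative analysis section describes the purpose of the tests as "To evaluate evidence of a statistically significant difference in our chosen effectiveness outcomes", and then states that "we will run a Student's paired t-test for barriers to adherence and adherence and a McNemar test for viral load, between T1 and T3". The level is fixed by "For all analyses, a significance level of 5% will be adopted"; sidedness is not given. Among the descriptive summaries, "barriers to adherence and adherence will be summarized with the minimum, the maximum, the mean, and the standard deviation", and viral load is reported as frequencies.

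The Study metrics and instruments section attaches a consequence to the table: "Not meeting the set thresholds for success, in this study, will signify that modifications are necessary before proceeding to a definitive trial". It does not exempt Objective 3. The Study design section says that a type 3 hybrid tests the implementation strategy and only observes effectiveness data.

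**The concern.** The rule has two weaknesses.

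- **Direction.** A test for a difference, judged by p ≤ 0.05 alone, is satisfied by change either way. Every numeric threshold for Objectives 1 and 2 in Table 3 is written as a lower limit (≥ or >). Only the Objective 3 entries have no sign.
- **Utility.** The same entry is the only threshold given for both halves of Objective 3. A p-value for T1–T3 change answers whether a mean or proportion moved. It says nothing about whether the measure is complete, has room to move, or varies in a way that can size the next trial. A sound measure of something that did not change gives p > 0.05, and a poor measure that drifts can give p ≤ 0.05.

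At stake is what the pilot tells the planners of the definitive trial about these outcomes. Taken with the consequence in Study metrics and instruments, a good measure could be flagged for modification because about 30 patients showed no significant change. A significance threshold also sits awkwardly with a design that says it only observes effectiveness.

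**Working it through.** The protocol gives no power figure or calculated sample size to reproduce. The 30 patients rest on a rule of thumb (Setting and participants). The check therefore applies the threshold as written.

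**Inputs**
- n = 30 patients (Summary; Setting and participants).
- n = 24, from the 80% retention benchmark (Feasibility): 0.80 × 30 = 24.
- α = 5% per test (Quantitative analysis). Two-sided is assumed, because the test is for a difference and sidedness is not stated.
- True standardised changes of 0.3 and 0.5 SD of the T1–T3 change. These are assumptions, since the protocol gives no effect size.

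**1. Smallest change that meets the threshold (paired t-test).** |mean change| / SD of change ≥ t(0.975, n−1) / √n.
- n = 30: 2.045 / 5.477 = 0.373
- n = 24: 2.069 / 4.899 = 0.422

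The value is the same for improvement and for worsening.

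**2. Chance of p ≤ 0.05 if the true change is a worsening.** Noncentral t with n−1 degrees of freedom and noncentrality δ√n:

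| Assumed worsening δ | n = 30 | n = 24 |
|---|---|---|
| 0 (no change), harmful direction only | 2.5% | 2.5% |
| 0.3 SD | 36% | 29% |
| 0.5 SD | 75% | 65% |

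**3. Viral load (McNemar, exact).** p = 2 × P(X ≥ k), with X binomial(m, 0.5), m discordant patients and k of them going one way.
- 6 against 0: 2 × (1/2)^6 = 0.031
- 8 against 1: 2 × (9 + 1)/512 = 0.039

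Six patients going from undetectable to detectable, with none the other way, meet the threshold as surely as six going from detectable to undetectable.

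**4. How often a sound measure misses the threshold.** With no true change, a paired t-test gives p > 0.05 in 95% of studies. By the symmetry of step 2, a true improvement of 0.3 SD is missed in about 64% (n = 30) or 71% (n = 24), and one of 0.5 SD in about 25% or 35%. None of these misses reflects on the quality of the measure.

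**5. What p leaves out for planning.** The 95% limits for the SD of change are s × √((n−1)/χ²), using the 0.975 and 0.025 quantiles of χ² on n−1 degrees of freedom and assuming normal changes.
- n = 30: 0.80 to 1.34 times the estimate
- n = 24: 0.78 to 1.40 times the estimate

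This uncertainty carries into the size of the next trial and cannot be read from the p-value.

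**The case against.** The strongest reply is that nobody would misread the result. The Objective 3 section calls undetectability a goal of treatment, the adherence item runs from very poor to excellent, and barriers are what the intervention sets out to address. Means, SDs and frequencies are planned alongside the tests, so the sign will be visible. Testing for a difference and reading direction from the estimate is ordinary practice. That stands: a reader might infer that the plan counts harm as success, and the protocol does not support that reading. The direction is an omitted condition in the rule.

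A reader might also infer that p alone decides which outcomes go forward. That is not stated either. The Aim and objectives section says usefulness is judged by observing the data. The Quantitative analysis section links targets for the ability to proceed to most metrics of Objectives 1 and 2. A missed threshold only signals modification.

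Part of what utility needs is already planned: I-Score missing-data and questionnaire non-completion rates, viral load frequencies, and minimum, maximum, mean and SD. Leaving further descriptive detail to an analysis plan would be normal.

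What this does not remove is the entry itself. Table 3 calls p ≤ 0.05 the success threshold for an objective that includes outcome utility, the consequence in Study metrics and instruments covers the set thresholds without exception, and the observational reading offers no rule to set against it. This is a criterion the protocol has fixed, so it is not detail left for later.

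**Conclusion.** The point holds in a limited form and is moderate in weight, since Objective 3 is secondary in a one-arm pilot whose primary outcome is acceptability. As written, the threshold is met by a mean change of 0.37 SD (n = 30) or 0.42 SD (n = 24) in either direction, or by six one-way viral load switches. It is missed 95% of the time by a sound continuous measure of an outcome that has not changed. These figures assume two-sided tests; a one-sided test in the favourable direction would settle the direction, but the protocol does not specify one.

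The 75% and 65% figures for a 0.5 SD worsening illustrate the literal rule under an assumed effect. They are not evidence that worsening is likely. The utility half is the firmer of the two: it depends on no assumed effect, because a p-value for T1–T3 change is the wrong kind of quantity for that question.

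**What to change.** In Table 3 and the Objective 3 paragraph of Quantitative analysis:

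- **Utility.** Remove p ≤ 0.05 as the success threshold. Use the completion and missing-data rates already planned, the share at the best category or undetectable at T1, and the SD of change and T1–T3 correlation, each with a 95% CI.
- **Promise.** Report the T1–T3 change with a 95% CI and require the favourable direction: higher self-rated adherence, fewer detectable viral loads, and fewer barriers. The I-Score direction should be written in once its scoring is fixed, because The I-Score intervention section says those details are still to come. Report significant change the other way as an adverse signal.
- **Patient management.** This row has the same bare entry and should be reworded at the same time.
- **Consequence.** State in Study metrics and instruments whether the modification rule applies to Objective 3.

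If the two-sided 5% test is kept for promise with direction added, false success per paired t-test under no change falls from 5% to 2.5%. Under the assumed 0.5 SD worsening it falls from 75% or 65% to below 0.001%.

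The cost is wording and a few descriptive statistics. No new data, patients or visits are needed.
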